## Abstract

**Background:**

Coronary artery disease remains the dominant cause of mortality in developed countries. While platelets have been recognized to play a pivotal role in atherothrombosis, the ideal antiplatelet regime after coronary artery surgery remains elusive.

The evolution of CABG has presently moved beyond technical improvements to involve modulation of pharmacologic management designed to improve patient outcomes. The aim of this trial will be to test the hypothesis that the addition of clopidogrel to patients with documented postoperative aspirin resistance will reduce the incidence of major cardiovascular events.

**Methods:**

Patients scheduled for isolated coronary artery surgery will be eligible for the study. Patients in whom postoperative multiple electrode aggregometry documents aspirin resistance will be randomized into two groups. The control group will receive 300 mg of aspirin. The dual antiplatelet group will receive 75 mg of clopidogrel in addition to 300 mg of aspirin. Patients will be followed for 6 months. Major adverse cardiac and cerebrovascular events (death from any cause, myocardial infarction, stroke, hospitalization due to cardiovascular pathology) as well as bleeding events will be recorded.

**Discussion:**

This will be the first trial that will specifically address the issue of dual antiplatelet therapy in patients undergoing coronary artery surgery who have been found to be aspirin resistant. In the event that the addition of clopidogrel proves to be beneficial in this subset of surgical patients, this study could significantly impact their future antiplatelet management.

This randomized controlled trial has been registered at the ClinicalTrials.gov website (Identifier NCT01159639).

## Background

Coronary artery disease is a health care issue of epidemic proportions, and has a profound impact on resource utilization. A quiescent atherosclerotic lesion may follow the course of progressive luminal encroachment, or succumb to an acute thrombotic event. Reduced *de novo* collagen synthesis and increased extracellular matrix metabolism contribute to weakening of the fibrous cap [1]. Platelet aggregation is a crucial component of this process. Coronary artery bypass grafting (CABG) remains the best management option for patients with severe multi-vessel coronary artery disease [2]]. It has been subjected to an unparalleled level of scientific scrutiny. The continuous trend toward improving patient outcomes following CABG stems from refinement of the technical aspects of the procedure, as well as optimization of the adjuvant pharmacologic therapy.

### Antiplatelet management following CABG

Platelet inhibition is paramount in the management of coronary artery disease. Antiplatelet drugs reduce mortality and the incidence of major vascular events in patients with a wide variety of vascular occlusive pathologies [3]. Their beneficial effects must be, however, balanced against the associated risk of bleeding. Acetylsalicylic acid (ASA) is currently recommended after CABG in order to improve long-term graft patency [4]]. The recommended doses range from 150 to 325 mg, with a trend towards clinical benefit when higher doses are utilized within the first year [4]]. There is no compelling evidence to support the superiority of clopidogrel to ASA monotherapy in optimizing graft patency following CABG [4]]. The mechanisms of action of thienopyridines and ASA differ, allowing for a cumulative anti-aggregative effect [3,5]. ASA irreversibly suppresses cyclooxygenase-1 activity thereby reducing thromboxane A2 production, whereas clopidogrel acts on the P2Y12 adenosine diphosphate (ADP) receptor to inhibit ADP-mediated platelet aggregation [6,7]. While dual antiplatelet therapy offers a reduction in atherosclerotic events in patients undergoing percutaneous coronary interventions, this benefit has not been reliably reproduced in other clinical settings [7,8]].

### Individual variability to antiplatelet agents

The incidence of interpatient variability to antiplatelet drugs depends upon the laboratory evaluation used to diagnose it [7]. Novel tools for quantifying drug induced platelet inhibition have brought into focus the individual variations in antiplatelet responses. This underscores the importance of identifying the optimal antiplatelet drug protocol in order to achieve the targeted level of anti-aggregation. Multiple electrode aggregometry (MEA) has been shown to be a useful instrument in the quantification of platelet inhibition by ASA [6]. Its mechanism of assessing platelet inhibition is based on changes in impedance on its sensor wires secondary to platelet adherence. Aspirin resistance has been suggested to range anywhere from 1 to 45% [7]. The efficacy of ASA absorption, TXA2 independent platelet activation pathways, COX-1 gene mutations, as well as ASA interactions with other medications have all been postulated to play a role in inducing aspirin resistance [9]. The response to ASA should best be viewed as a continuous variable. Dichotomizing patients into responders or non-responders is, however, suitable for scientific research and is commonly employed for this purpose [7]. The presence of ASA low-responsiveness has been linked to an increase in cardiovascular morbidity [9]. The clinical correlation of individual patient refractoriness to ASA with an increased incidence of cardiovascular complications is fundamental to the present study. This will be, to the best of our knowledge, the first prospective randomized study that will aim to evaluate whether the combination of ASA and clopidogrel in ASA-resistant CABG patients offers a clinical benefit. Our hypothesis that a dual antiplatelet regime will improve patient outcomes in this setting stems from the convergence of the clinical impact of ASA resistance and the benefit gained from adding clopidogrel to ASA in certain clinical scenarios.

## Methods

### Study population

All consecutive patients aged 18 years or more, scheduled for an elective surgical myocardial revascularization procedure using cardiopulmonary bypass over the study period, at the University Hospital Center Zagreb, will be screened for the study. Written informed consent will be obtained from all patients prior to enrolment into the study. The preoperative exclusion criteria will include valvular pathology warranting surgical correction, critical preoperative state, inability to provide informed consent, reoperation, any medical condition for which dual antiplatelet therapy is indicated, redo-CABG, off-pump CABG, preoperative antiplatelet therapy other than ASA or clopidogrel, preoperative anticoagulation with coumadin and history of cerebrovascular accidents. Furthermore, patients who require postoperative anticoagulation, intra-aortic balloon pump support, or who die prior to postoperative day 4 will not be included into the study. All other consecutive isolated CABG patients will be screened for the study. Those patients who exhibit aspirin resistance on their MEA evaluation on postoperative day 4 will then be randomized into two groups.

### Ethics

The Ethics Committee of the University Hospital Center Zagreb has evaluated and approved the conduct of this study (No. 01/001/VG) on 23 June 2010. Ethical standards in line with the Declaration of Helsinki involving research on human subjects will be strictly adhered to. This protocol complies with the CONSORT guidelines [10].

### Sample size

An exact binomial test power analysis was performed in order to estimate the approximate sample size required to test the null hypothesis. The minimum effect size was 10%. Accounting for a maximum estimated 10% loss to follow-up, a total of 219 patients will be required to test the null hypothesis with an α value of 0.05 and a power of 0.8.

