### Randomization of patients and interventional strategy

All post-CABG patients in whom none of the postoperative exclusion criteria have occurred will undergo MEA analysis on postoperative day 4. Patients found to have evidence of ASA low-responsiveness, as defined by an ASPI test ≥ 30 AUC, will undergo randomization into either the control group or the dual antiplatelet therapy (dAPT) group. Assignment to either group will be performed by random allocation using randomization software [15]. Patients in the control group will continue to receive 300 mg of ASA in accordance to our hospital’s standard post-CABG antiplatelet management strategy. Patients in the dAPT group will, conversely, be subjected to augmentation of their antiplatelet regime by receiving 75 mg of clopidogrel in addition to the 300 mg of ASA. A flowchart depicting the screening and randomization protocols is shown in Figure 1.

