### Statistical analysis

The continuous data will be presented as mean values ± standard deviation (SD) or medians with their respective interquartile range. Categorical variables will be presented as absolute numbers with percentages. Analyses of continuous data between different groups of patients will be performed using the Mann-Whitney *U*-test. Differences between categorical variables will be evaluated with Fisher’s exact test. A two-tailed *P*-value will be used amd *P* < 0.05 will be considered significant for all deployed statistical calculations. The data will be processed using the Statistica 9 software package (StatSoft Inc., Tulsa, USA).

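### A total of 219 does not give the two-arm Fisher comparison 80% power for a 10-point MACCE difference unless the control rate is about 11%

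*Protocol article*

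**What the plan says.** The Sample size section names its method: "An exact binomial test power analysis was performed in order to estimate the approximate sample size required to test the null hypothesis". Its inputs are an effect ("The minimum effect size was 10" per cent, not said to be absolute or relative), an attrition allowance ("Accounting for a maximum estimated 10% loss to follow-up"), and the error rates ("with an α value of 0.05 and a power of 0.8"). The result is that "a total of 219 patients will be required to test the null hypothesis with an α value of 0.05 and a power of 0.8". No control-arm MACCE rate, reference proportion or allocation ratio appears.

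Elsewhere the design has two arms. Under Randomization of patients and interventional strategy, eligible patients "will undergo randomization into either the control group or the dual antiplatelet therapy (dAPT) group". Under Outcome definitions, the primary endpoint is MACCE incidence under the two strategies. Under Statistical analysis, "Differences between categorical variables will be evaluated with" Fisher's exact test, and "A two-tailed *P*-value will be used amd *P* < 0.05 will be considered significant".

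**The concern.** An exact binomial test, taken at its name, compares one proportion with a known constant. The planned analysis compares two estimated proportions, so the second arm adds sampling error and the patients are divided between arms. A total sized for the first problem is generally too small for the second. The power for a 10-point difference between two proportions also depends strongly on the control rate, so a single power of 0.8 has no meaning until that rate is fixed.

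At stake is how a non-significant MACCE result will be read. Readers told that power was 0.8 would take it as fair evidence that clopidogrel does not give a 10-point benefit. If power was really below one half, that reading is wrong.

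**Working it through.** **Inputs.** From Sample size: total 219, effect 10%, α 0.05, power 0.80, loss 10%. From Statistical analysis: two-sided testing, Fisher's exact test. From the randomisation section: two arms. Assumed: 1:1 allocation, and a range of control rates.

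**Step 1. Where 219 may come from.**

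*Route A, one-sample exact binomial.* Take p0 = 0.50 against 0.60, with a two-sided test at 0.025 per tail. The smallest n with power of at least 0.80 is 199 (power 0.804, actual α 0.047). Then 199 × 1.1 = 218.9, so 219. The value p0 = 0.50 is not in the article, and it is not unique: 0.45 against 0.55 also gives n = 199. Dividing by 0.9 instead of multiplying by 1.1 gives 199 / 0.9 = 221.1, so 222.

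*Route B, two-sample formula, 20% against 10%.* With mean rate 0.15:

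n per arm = [1.960 × √(2 × 0.15 × 0.85) + 0.842 × √(0.20 × 0.80 + 0.10 × 0.90)]² / 0.10² = 198.96, so 199 per arm.

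Again 199 × 1.1 = 218.9, so 219, but now **per arm**, or 438 in total. Exact Fisher power with 219 analysed per arm is 0.81.

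Route A fits the named test better. Under either route, a **total** of 219 does not match the planned comparison.

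**Step 2. Analysable patients.** 219 × 0.9 = 197.1, so about 197, split 99 + 98.

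**Step 3. Power of the planned test.** Power = Σ over all (x, y) of Bin(x; n₁, p_C) × Bin(y; n₂, p_T) × 1[two-sided Fisher P < 0.05], with p_T = p_C − 0.10, fully enumerated.

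| Control rate | Dual-therapy rate | Power, 99 + 98 | Power, no loss (110 + 109) |
|---|---|---|---|
| 10% | 0% | 0.94 | 0.97 |
| 11% | 1% | 0.84 | 0.89 |
| 12% | 2% | 0.76 | 0.82 |
| 13% | 3% | 0.69 | 0.75 |
| 15% | 5% | 0.59 | 0.65 |
| 20% | 10% | 0.45 | 0.49 |
| 30% | 20% | 0.32 | 0.36 |
| 50% | 40% | 0.27 | 0.29 |

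With 99 + 98, power at 11.5% is 0.795, so the 80% crossing lies just below that. The implied relative reduction is 10/11 = 91% at an 11% control rate and 10/12 = 83% at 12%. Below a 10% control rate, a 10-point reduction is impossible.

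**Step 4. If 10% is relative.** With p_T = 0.9 × p_C and 99 + 98, power is 0.04 at a 10% control rate, 0.05 at 20%, 0.06 at 30%, 0.07 at 40% and 0.10 at 50%.

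**Step 5. What 219 can detect.** With 99 + 98, about 80% power is reached for these absolute differences:

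- 15% control: 12 points (power 0.82)
- 20% control: 14 points (power 0.81)
- 30% control: 17 points (power 0.80)

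**Step 6. Total needed for 80% power at 10 points** (continuity-corrected two-sample formula, divided by 0.9): 238 at an 11% control rate, 356 at 15%, 487 at 20%, 696 at 30%. These show the size of the gap; they are not a proposal to recruit more.

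**The case against.** Three points on the other side have force.

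First, the origin of 219 cannot be proved. A reader might infer that the article demonstrably used a one-sample test against 50%. The article does not support that: it names the test but gives no reference proportion, and two other sets of inputs also reach 219. This limits the diagnosis to a probable one. It does not affect Step 3, which depends only on the total, the two arms and the named test.

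Second, low control rates cannot be excluded. Follow-up is six months, surgery is elective, and the Study population section removes several high-risk groups. At 10% to 11% the stated power is met or exceeded, and at 12% to 15% a significant result is still the likelier outcome if the effect is real. A reader might infer that the trial is underpowered whatever the event rate, or that a null result is always the expected one. Neither holds: a null result is the more likely one only at control rates of about 20% or more. But the power at low rates requires dual therapy to remove more than four fifths of a composite that includes all-cause death and cardiovascular rehospitalisation, and the article states no such assumption.

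Third, a journal article condenses, so the control rate may stand in a fuller protocol. Its absence is not the finding. The finding is the mismatch between what the article does state: a binomial method, a total of 219 and power of 0.8, against a two-arm Fisher comparison. Nothing else in the article reconciles them.

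**Conclusion.** The point stands. For a 10-point absolute difference, a total of 219 delivers the stated 80% power only if the control MACCE rate is about 11% (about 12% with no loss). From 15% to 50%, power falls from 0.59 to 0.27. If the 10% is relative, power is about 4% to 10% for control rates of 10% to 50%.

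These figures rest on 1:1 allocation, 197 analysable patients and assumed control rates. The calculation of power for the named test is firm; the explanation of how 219 arose is only probable. This needs correction because it is the stated power of the primary comparison.

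**What to change.** Keep 219 patients and replace the Sample size paragraph with a two-sample calculation for Fisher's exact test. It should:

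- state the assumed control MACCE rate and the allocation ratio;
- state that the 10% is an absolute difference;
- replace the 80% claim with what 219 delivers at that rate, for example about 45% power for 20% against 10%, or about 80% power for a difference of 12 points at a 15% control rate, 14 points at 20% or 17 points at 30%;
- state that a non-significant result will not be read as absence of a 10-point benefit.

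The cost is a one-paragraph text amendment and a less favourable stated power. No extra patients are needed, and treatment does not change.

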### Aspirin low-responsiveness

The ASPI test evaluates cyclooxygenase-dependent platelet aggregation (using arachidonic acid) that is sensitive to aspirin. Our definition of low response to ASA will be based upon our own published experience with multiple electrode aggregometry in a similar population of patients [11]. In brief, patients in the aforementioned study were divided into quartiles with respect to their ASA responsiveness, and those in whom the ASPI test was greater than the 75^th^ percentile of the entire cohort (that is, area under the curve, AUC ≥ 30 units) were defined as being ASA low-responders [11]. This definition has been corroborated by published data from other sources [12-14].

### Randomization of patients and interventional strategy

All post-CABG patients in whom none of the postoperative exclusion criteria have occurred will undergo MEA analysis on postoperative day 4. Patients found to have evidence of ASA low-responsiveness, as defined by an ASPI test ≥ 30 AUC, will undergo randomization into either the control group or the dual antiplatelet therapy (dAPT) group. Assignment to either group will be performed by random allocation using randomization software [15]. Patients in the control group will continue to receive 300 mg of ASA in accordance to our hospital’s standard post-CABG antiplatelet management strategy. Patients in the dAPT group will, conversely, be subjected to augmentation of their antiplatelet regime by receiving 75 mg of clopidogrel in addition to the 300 mg of ASA. A flowchart depicting the screening and randomization protocols is shown in Figure 1.

**Figure 1 F1:**
[figure not shown]
**Flowchart detailing the screening algorithm for patient recruitment, followed by subsequent randomization into the aspirin monotherapy or dual antiplatelet therapy groups.** CABG, coronary artery bypass grafting; MEA, multiple electrode aggregometry; ASPI, cyclooxygenase dependent platelet aggregation, AUC, area under the curve; ASA, acetylsalicylic acid; MACCE, major adverse cardiac and cerebrovascular events.

### Preoperative antiplatelet therapy management

Preoperative antiplatelet therapy is managed by the referring cardiologist. It almost uniformly consists of 100 mg of ASA and this is continued up to the day of surgery. Some patients receive clopidogrel in addition to ASA in the preoperative period. Clopidogrel will be discontinued 5 days prior to the scheduled revascularization procedure. All patients included in the study will have received antiplatelet therapy for no less than 14 days prior to enrolment.

### Perioperative management

The perioperative management of study patients will not deviate from our hospital’s standard preoperative anesthetic regime, which includes diazepam and morphine prior to induction of anesthesia. Endotracheal tube, urinary catheter, radial artery and pulmonary artery catheters will be inserted. Our protocol will consist of induction and maintenance of anesthesia with midazolam, fentanyl and pancuronium bromide. This will be complemented with sevoflurane inhalation. The initial ventilator settings will consist of a tidal volume of 8 ml/kg, and a respiratory rate of 12 breaths per minute. Systemic heparinization with a target-activated clotting time > 480 seconds will be utilized, followed by full reversal with protamine after decannulation. The cardiopulmonary circuit will include the Medtronic Affinity Trillium membrane oxygenator, venous reservoir and PVC tubing (Medtronic, Minneapolis, USA) and a Stoeckert III roller pump (Stoeckert, Munich, Germany). The ascending aorta and right atrium will be cannulated for cardiopulmonary bypass (CPB). The CPB flow will approximate 2.4 L/min/m^2^. Every effort will be made to maintain the mean systemic pressure during CPB between 60 and 80 mmHg. Vasopressors will be used as needed in order to achieve the target mean pressure. The patient’s temperature will be allowed to drift down to 32 to 34°C. Myocardial protection will be based upon a combination of antegrade and retrograde cardioplegia, coupled with topical cooling. Both the coronary and the proximal aortic anastomoses will be performed on an arrested heart, during a single period of aortic cross-clamping. Weaning from CPB will typically be performed without inotropic support. In patients in whom the cardiac index will remain below 2.2 L/min/m^2^, dobutamine will be administered. Norepinephrine will be instituted if dobutamine produces excessive vasodilatation. Escalation of vasoactive support, if necessary, will include the addition of another inotrope, an intra-aortic balloon pump or mechanical circulatory assistance.

Postoperative medications will typically include a beta blocker, a hydroxy-methyl-glutaryl-CoA reductase inhibitor and a diuretic. Electrolytes will be supplemented as indicated. An ACE inhibitor will be instituted, as tolerated. Peptic ulcer prophylaxis will be universally implemented, and continued for six weeks postoperatively. Non-steroidal anti-inflammatory drugs will generally not be administered in the early postoperative period. The antiplatelet regime will be based upon the previously mentioned randomization protocol.

### Blood sampling

Blood samples for MEA measurements will be obtained on postoperative day (POD) 4 via peripheral venipuncture. The search for an ideal anticoagulant for blood samples used for the quantification of platelet function is still ongoing. Heparin will be the anticoagulant used in the present study [16,17]. Blood will be collected in 4 ml heparin (Lithium Heparin 68 IU)-coated BD Vacutainer plastic tubes. Routine laboratory evaluations will be performed and recorded preoperatively and on POD 4. The same person, who has no direct involvement in either patient care or postoperative follow-up, will perform all MEA measurements. Blood samples will be allowed to rest for 30 minutes after blood withdrawal and MEA will be performed subsequently.

### Multiple electrode aggregometry (MEA)

Whole blood aggregability will be determined using a new generation impedance aggregometer (Multiplate® analyzer, Dynabyte Medical, Munich, Germany). The method has been described in detail previously, and has already been validated [18]. In brief, the principle underlying MEA is that platelets are non-thrombogenic in their resting state, but have the potential to present multiple surface receptors when activated, which enables them to attach to a variety of surfaces. The accumulation of platelets on the Multiplate sensor wires will increase the electrical resistance between them. This variability in impedance, which is expressed in arbitrary AUC units, is the MEA parameter with the highest diagnostic value [18,19]. The analysis takes 3 minutes for incubation and 6 minutes for the post-stimulation measurement. Platelet aggregation was determined in response to stimulation with arachidonic acid with a final concentration of 0.5 mM (ASPI test designed to evaluate ASA effect) and ADP with a final concentration of 6.4 μM (ADP test designed to evaluate thienopyridines, that is, clopidogrel).

